Our current initiative in Alberta, Canada – the Integrating Prevention into Connect Care for Health (IPiC-Health) project has two-fold objectives: (a) to integrate SBIR, to identify and address tobacco use, alcohol use, and insufficient physical activity, within Connect Care-facilitated patient care workflows in a variety of acute and ambulatory care settings, as a routine component of care; and (b) to demonstrate the feasibility and impacts, on patient outcomes and health system costs, of SBIR implementation within these settings. The IPiC-Health initiative intends to strengthen the quality and generalizability of effectiveness evidence and implementation guidance to inform spread and scale out of the approach to a wide variety of clinical programs. This methodological paper describes the research plan to rigorously evaluate the implementation and effectiveness outcomes of SBIR intervention.

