## Overview of the Program

### Description of intervention and settings

The IPiC-Health initiative is a three year project (January 2023-December 2025) that engages a variety of ambulatory and inpatient healthcare sites and providers in delivering SBIR for health promotion as a routine component of patient care. These sites provide care to patients with a variety of acute and chronic health issues, including rheumatological conditions, surgery, diabetes, pneumonia, asthma, cardiac diseases, trauma, and geriatrics. This initiative leverages the province-wide electronic (“Connect Care”) clinical information system to help integrate the SBIR actions and documentation sustainably into routine care. Screening involves using standardized screening questions to identify patients who use commercial tobacco, consume alcohol at levels that increase risk, or who participate in insufficient physical activity [28,29,30,31,32,33]. The brief intervention is a conversation that providers have with patients who have elevated risk on one or more of those modifiable risk factors. The brief conversation aims to educate patients about the health risks, identify patient readiness to consider a change in behaviour, and to encourage them to take action. Providers are then able to offer educational resources (e.g., a brochure containing QR codes/links to relevant websites) that provide behaviour change information and support. Providers can also refer patients to support services available in their community (e.g., Alberta Quits program for tobacco cessation) (Figure 1).

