Patient follow ups: Effectiveness of SBIR intervention	Patients’ behavior change status for both control and intervention patient groups	Intention to change behavior, awareness about the problem, commitment to action, uptake to referral programs, active modification of behavior (such as quit attempt, reduce/quit tobacco use, reduce/stop alcohol intake, and initiate/increase physical activity). Covariates for effectiveness outcomes: Sociodemographic/socioeconomic (such as age, sex, marital status, ethnicity, education, employment, income, rurality, immigration-related factors) and overall physical and mental health status.	Primary data collection from patients.	Follow-up telephone interview at six months of index hospitalization discharge/visit. Data collection tool will include the questionnaires guided by the Prochaska model of change process and the risk factor screening questions included in the Connect Care

Healthcare resource use	Hospital readmissions and emergency visits for both control and intervention patient groups	Hospital readmissions and emergency visits during the year after index hospitalization discharge /visit. Reasons/diagnosis for readmissions and emergency visits, and family physician/primary care visits within 1-year of discharge/visit and diagnoses/comorbidities at the time of recruitment to 1-year of index hospitalization discharge/visit.	Administrative health databases: Discharge Abstract Database, National Ambulatory Care Reporting System, and physician claim databases	Data from multiple databases will be accessed through Data and Analytics. and will be linked with the follow-up interviews using the personal health numbers.

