## Research plans for evaluation of intervention effectiveness outcomes

*Study design and participants:* We use a quasi-experimental study design (pre-post with a comparison group). The intervention group are patients from participating units during the SBIR implementation period who screen at increased risk on any of the three risk factors and received brief intervention and referral support. The comparison group are patients from the same units, during a 6-month pre-implementation period, identified as having increased risk on any of the three risk factors, but who do not receive the SBIR intervention.

Study inclusion criteria for the target patient population to be enrolled in the effectiveness study include: Adult patients (>18 years) who are residents of Alberta, have the ability to engage in the SBIR process and data collection, and are attending the participating sites during the study period. Research assistants enroll the eligible patients in the study after they provide informed consent. The patients with severe disease conditions (i.e., unconsciousness and end-stage care) or those with mental or cognitive incapacity are excluded.

*Outcome definition and measurement for both groups:* Key outcomes are patient behaviour change in relation to the modifiable risk factors and health care utilizations in the year after recruitment to the study. Measurement of patient’s behaviour changes involves: questions on patients’ intention to change behaviour, their uptake of referral services (for those who received referrals), and changes in risk level as measured using the same risk factor screening tools used during the SBIR intervention. We also ask patients about tobacco use reduction, tobacco quit attempts, seven- and 30-day tobacco abstinence. The data are being collected via telephone interviews at 6 months follow-up after the index clinic visit, or discharge from a hospital stay, during which the patient was recruited into the study. A sample of participating patients are also called at 1 month after their hospital/clinic visit to ask them about their experience of the SBIR intervention.

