Cost-effectiveness analysis will document the economic value of the SBIR intervention in order to communicate that value to decision-makers. Cost reduction/avoidance within one year, attributable to SBIR, will be estimated based on the reduction in 1-year readmissions and emergency visits, compared to the non-intervention comparison group. Estimates of this economic impact will be provided by applying hospitalization and emergency visit cost data, provided by Canadian Institute of Health Information (CIHI), to the utilization estimates from the above-mentioned models. Intervention implementation cost data are being collected throughout the project.

*Ethical considerations:* This study has received ethics approval from the Health Research Ethics Board of Alberta – Community Health Committee- at the University of Calgary (HREBA.CHC-22-0058).

*Involvement of people with lived experience:* IPiC-Health project has 7 patient advisors, who closely work with the research and innovation team of IPiC-Health project. The patient advisors provide insights based on lived experience to inform SBIR pathways, the research and implementation plan, development of resources, brief conversation scripts, and provide advice on acceptability and appropriateness on all aspects of the research and intervention. The Patients advisors consist of individuals connected to the Alberta Strategy for Patient Oriented Research SUPPORT Unit (AbSPORU) and Patient and Community Engagement Research (PaCER) | University of Calgary-trained patient researchers who have lived experience of care in Alberta’s patient care settings and/or with the risk factors targeted by the SBIR intervention.

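### The costing prices only readmissions and emergency visits, so it does not measure the change in health system cost named in the objective and may misstate the saving

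*Protocol article*

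**What the plan says.** The last paragraph of the Background gives objective (b): "to demonstrate the feasibility and impacts, on patient outcomes and health system costs, of SBIR implementation within these settings".

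The cost-effectiveness paragraph, under Research plans for evaluation of intervention effectiveness outcomes, says how the cost part will be answered: "Cost reduction/avoidance within one year, attributable to SBIR, will be estimated based on the reduction in 1-year readmissions and emergency visits", relative to the comparison group. The money value comes from "applying hospitalization and emergency visit cost data". The paragraph ends with "Intervention implementation cost data are being collected throughout the project" and does not say what those costs contain or how they enter the result.

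Table 1, in the healthcare resource use row, also lists "family physician/primary care visits within 1-year of discharge/visit". The sources for that row are "Discharge Abstract Database, National Ambulatory Care Reporting System, and physician claim databases", and the row covers both groups.

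On referral, Description of intervention and settings says: "Providers can also refer patients to support services available in their community". The design section says that control patients are not offered brief intervention or referral. The effectiveness section defines intervention patients as those who received both. Uptake of referral services is asked at the 6-month telephone interview, and only of patients who were referred.

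**The concern.** The objective concerns the cost to the health system. The rule counts two kinds of hospital-based use, both of which the intervention is hoped to reduce. Two other kinds of use that may change are left out.

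- **Primary-care visits.** The study already plans to obtain these for one year in both groups, but they drop out between Table 1 and the costing.
- **Referral services.** The two groups differ in exposure to these by construction. The Discussion (Disadvantage) says that direct referral pathways within the provincial health system exist for smoking cessation and high-risk alcohol use, so at least part of this use falls on the health system.

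If care moves from hospital to community services, the planned figure records the hospital part of the move and misses the rest. The article says that the utilization outcomes will support spread and scale decisions by administrators. A partial figure presented as cost-effectiveness could be read as the net value to the health system.

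**Working it through.** The article gives no unit cost, visit rate or expected saving, so there is no stated figure to reproduce. The check sets the passages side by side and then uses an accounting identity.

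**Which use is measured and which is priced**

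| Component | Measured? | Priced in the costing paragraph? |
|---|---|---|
| Readmissions, 1 year | Yes, administrative data, both groups | Yes |
| Emergency visits, 1 year | Yes, administrative data, both groups | Yes |
| Primary-care visits, 1 year | Yes, physician claims, both groups (Table 1) | No |
| Referral-service use | In part: self-reported uptake at 6 months, among those referred | No |
| Implementation cost | Being collected; content not described | Role not stated |

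**Identity, per patient over one year**

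Net saving = (readmissions avoided × unit cost) + (emergency visits avoided × unit cost) − (change in primary-care visits × unit cost) − (referral uptake × unit cost) − implementation cost.

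The planned saving is the first two terms. Before implementation cost, its error is the third and fourth terms together.

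- The referral term takes something away if intervention patients use any priced service that controls do not. That follows from who is offered referral.
- The primary-care term can have either sign. No passage names primary care as a referral target or predicts more visits.

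**Illustration on assumed values only**

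None of these inputs comes from the article. Assumed relative unit costs are readmission 1, emergency visit 0.05, primary-care visit 0.01 and referral episode 0.03. Assumed effects are 0.01 to 0.03 readmissions and 0.02 to 0.05 emergency visits avoided per patient.

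- Planned saving, low: 0.01 × 1 + 0.02 × 0.05 = 0.011. High: 0.03 × 1 + 0.05 × 0.05 = 0.0325.
- No change in visits, 10% uptake: omitted cost 0.10 × 0.03 = 0.003, which is 9% (0.003/0.0325) to 27% (0.003/0.011) of the planned saving.
- 0.5 more visits, 10% uptake: 0.5 × 0.01 + 0.003 = 0.008, which is 25% to 73%.
- 1 more visit, 30% uptake: 0.01 + 0.30 × 0.03 = 0.019, which is 58% to 173%. Above 100% the saving becomes a net cost.
- 0.5 fewer visits, no uptake: −0.005, so the planned figure understates the saving by 15% to 45%.
- No change and no uptake: 0%.

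The illustration shows that the omitted terms can matter and that their combined sign is open. It does not estimate their size in this study.

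**The case against.** The strongest reply is that this is a condensed article. Costing perspective, effect measure and netting rules usually sit in a fuller plan. In Table 1 the outcome cell names only readmissions and emergency visits; primary-care visits share a measures cell with diagnoses and comorbidities, so they may be meant for description or adjustment. The article also already calls the quantity cost reduction or avoidance. Referral costs may be small: the Discussion says some referrals were informational only, and Expected Results and Applicability reports low brief-intervention rates and unclear referral pathways. Referral uptake is self-reported, with about 50% of patients responding to follow-up.

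Much of this stands. The text is silent on whether implementation cost is netted off, whether it covers some referral cost, and which effect measure is used. That silence cannot be read as exclusion, so it does not follow that no behaviour outcome will enter the analysis. Referral uptake at 6 months is also not one-year volume or cost.

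A reader might go further and infer that the saving is overstated, or that SBIR is designed to raise primary-care visits. The documents support neither. The direction for primary care is unknown, and the net direction depends on figures the article does not give. Nor does the one-year horizon prove a bias in favour of SBIR: the article's own remark is that its follow-up may underestimate the ultimate effect.

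The reply does not remove the mismatch. The article does not leave the costed use open. It names two categories and their unit costs, and these are narrower than both the objective and the use that Table 1 plans to collect.

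**Conclusion.** The point holds as a mismatch between objective and costing. As written, the rule estimates avoided hospital and emergency cost, not the change in health system cost, and it may misstate the saving. Omitted referral-service use points towards overstatement, assuming that intervention patients take up some services that the health system pays for. The direction for primary-care visits is not known from the documents.

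No magnitude can be derived. The range from a 45% understatement to a 173% offset rests wholly on assumed costs and effects. The behaviour-change comparison is not affected. This is a low-cost improvement to a secondary part of the evaluation, and it can still be made: the article says analysis will follow once the data are complete.

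**What to change.** In the cost-effectiveness paragraph:

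1. Add the adjusted between-group difference in one-year physician-claims visits to the costed use, and name the source of the unit cost per visit.
2. Include referral-programme uptake multiplied by programme cost as a sensitivity range, as far as the 6-month self-report allows, and say that it is not one-year use.
3. State what the implementation cost contains, net it against the result, and make sure that referral cost is not counted twice.

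If this is not done, label the result avoided hospital and emergency cost and do not present it as health-system cost-effectiveness.

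The visits come from databases already planned for linkage. The added work is a unit cost for visits, an external cost for referral programmes, and a model for visit counts, because the article names only time-to-event models for health care use. The price is a wider interval and possibly a less favourable net figure. Relabelling alone costs nothing but leaves the health-system cost objective only partly answered.

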## Discussion

### Advantage

The strengths of our method center around the evaluation of both effectiveness and implementation outcomes in a single study to generate effectiveness and implementation evidence that is critical for integrating care in routine practice. Specifically, this study measures the effectiveness of patient behavior changes in response to the SBIR intervention, while simultaneously evaluating the feasibility and acceptability of implementation through process-oriented, mixed methods, guided by implementation science frameworks. We engage with multiple clinical stakeholders (patients, providers, and clinical managers or leaders) at an early stage and throughout the implementation, which allows us to understand potential barriers/facilitators and informs the selection of appropriate implementation strategies for real-world implementation and sustaining the intervention. In addition to the quantitative assessment of implementation feasibility, acceptability, and appropriateness, process-oriented qualitative assessment during the implementation allows to seek feedback from patients and providers or site managers or leaders on implementation potential in their setting and adaptation needs for a better fit in their context, and understand how and why interventions may vary in effectiveness across settings [27,43,44,45]. This approach focuses on identifying why strategies work (or not) and informing the implementation needs or co-plan strategies going forward to support the adoption, adaptation and sustainability of the intervention, as opposed to just demonstrating their impact on reach, adoption, and fidelity [27,43,44,45,46]. The concurrent gathering of both effectiveness and implementation data is critical, otherwise, we may be unaware of crucial contextual factors related to the success or failure of the interventions.

Most of the previous studies of SBIR focused on alcohol use in primary care settings and mainly assessed effectiveness of SBIR in reducing alcohol consumption [25,47,48,49]. However, very few studies have assessed effectiveness outcomes through an equity lens (e.g., age, socioeconomic status, race) and performed ongoing assessments of barriers and facilitators alongside iterative refinement of implementation processes [25]. In addition, the majority of these studies were randomized controlled trials (which, while rigorous, often provide limited guidance on real-world implementation). Other studies have relied on weaker study designs (such as those without control groups), and frequently lacked comprehensive measurement, and the use of theoretical frameworks for evaluation [25]. Our effectiveness-implementation hybrid evaluation approach addresses the existing gaps by employing a pragmatic quasi-experimental study design (with a control group), integrating mixed methods and implementation science frameworks to systematically assess both outcomes/effectiveness and implementation processes. This approach increases the feasibility of conducting the study in a real-world setting while maintaining the rigour and generalizability of the evidence and provide evidence-informed implementation guidance to help integrate this intervention as routine patient care practice in real-world healthcare settings. This dual focus on effectiveness and implementation outcomes is an evidence-based approach that has been used in different studies conducted in various healthcare settings [26,27,43,50]. To our understanding, the use of this approach is new in the context of evaluating EHR-facilitated SBIR intervention in healthcare settings to address the modifiable risk factors for cancer and chronic diseases of patients.

The judicious integration of evaluation of effectiveness and implementation outcomes in a single study can help practically integrate research in healthcare settings and address healthcare needs. This provides more useful information for decision-makers, increases the generalizability of the findings, and improve the speed of moving research findings into routine adoption, compared to pursuing these lines of research independently [26,27,43,50]. However, keeping effectiveness and implementation research separate and sequential overlooks complexity, limits the generalizability and slows down the translation of knowledge into routine practice [26,27,43]. Effectiveness research alone is more affected by generalizability because of a failure to document and attend to contextual factors influencing effectiveness.

### Disadvantage

Given the different, multiple priorities and methods involved in evaluating effectiveness and implementation outcomes, the IPiC-Health study has potential challenges that require special attention, which are similar to the existing literature that used hybrid study designs [26,27,36,44,45,46,47,51,52,53]. The focus on evaluating both outcomes, using mixed methods, can lead to competing priorities and resource allocation challenges, and the potential of de-prioritization of either of the outcomes or associated activities [27,43,46,51]. Given the complexity of and multifaceted nature of the study design and implementation process, clinical buy-in or engagement, defining and measuring implementation outcomes, and identifying and reporting implementing strategies can be challenging [27,46,52]. While local adaptation can improve contextual fit and uptake, it can produce differences in fidelity within local adaptations; thereby leading to variations in the effectiveness of the intervention. Collection and organization of various types of quantitative and qualitative data from multiple, different sources at multiple times within a complex clinical implementation context requires ongoing attention from multiple members or experts [51]. To mitigate these challenges, the IPiC-Health study involves a specialized, interdisciplinary project team, including expertise in implementation science, methodology, ethical considerations, data integration, clinical contexts, and project management [36]. The project team continuously collaborates with the participating settings to ensure a smoother implementation process, uses electronic medical records and health administrative data, and documents the ongoing interaction between project and clinical teams to reduce the burden of data collection [35,52,53,54]. Additionally, project staff are embedded in research sites to perform the research participant recruitment and primary data collection, and provide implementation supports [35,36]. The project team carefully plans, executes, and monitors the study activities regularly to adequately address the needs of both aspects of research and balance internal and external validities.

Self-administered questionnaires are used to assess risk factors in the control group. These same questionnaires are integrated into the Connect Care system to support provider-led screening within routine clinical workflows, which are used for risk factor screening in the intervention group. Social desirability bias can be present when patients respond to questions about their health-related behaviours. However, we have no reason to expect the bias in responses to the risk factor questions will be different between the control and the intervention groups. Additionally, the follow ups at 6 months and 12 months to measure behavior change and healthcare use outcomes, respectively, may underestimate the intervention’s ultimate effects, as the outcomes may take a longer period to manifest. However, existing literature has demonstrated measurable changes within these timeframes [40,41,42,55], and demonstrating near-term impact was a key criterion for the grant funding mechanism supporting this project.

We acknowledge that effective prevention care ideally addresses the full prevention continuum; however, this was beyond the scope of the current project, which focused on establishing improved processes for delivering preventionrelated care within hospital settings. Within our intervention approach, patients who expressed interest in behavior change were encouraged and supported to access relevant communitybased services and supports. Because direct referral pathways within the Alberta health system were available only for certain behavior change needs (specifically smoking cessation and highrisk alcohol consumption), some referrals were necessarily informational and patientdirected. Hospital-anchored prevention pathways are simply one of many on-ramps that need to be made available to patients/people to support the promotion of health and the reduction of illness and its related health system costs. Ultimately, health promotion through primary care and through intersectoral partnerships to create supportive health environments in community will be vital to improving population health and reducing avoidable hospitalization.

